### Outcome Measures

Participants will complete an online survey via REDCap at preround, postround, and 3-month follow-ups, which will collect demographic information and measures of staff well-being, compassionate care, and organizational factors. Demographic data will include age, sex, ethnicity, profession, length of time in profession, workload and typical roster, and length of employment at the Hospital.

Staff well-being will be measured using the Maslach Burnout Inventory–Human Services Survey (MBI-HHS) [27]. The MBI-HHS is a reliable and validated 22-item measure that measures burnout using 3 subscales: Emotional Exhaustion (α=.90), Depersonalization (α=.79), and Personal Accomplishment (α=.71), on a 7-point scale ranging from “never” to “everyday.” Compassionate care will be measured using the Schwartz Centre Compassionate Care Scale (SCCCS) – provider version [28,29]. The SCCCS consists of 12 items answered on a 10-point scale and has been shown to be reliable and valid for use with patients (α=.98) [29]. Organizational culture will be assessed using the Culture of Care Barometer – version 2 (CoCB-v2) [27]. The CoCB-v2 is a reliable and valid measure that consists of 30 items across 4 subscales: Organizational Values (α=.93), Team Support (α=.93), Relationships With Colleagues (α=.84), and Job Constraints (α=.70) [30,31].

In addition to these outcome measures, participants will be asked to complete the standard Schwartz Rounds Evaluation Survey at the end of each Round. This survey includes 10 questions answered with no, yes, or not sure; a question asking the participants to rate the Round overall as either poor, fair, neutral, good, or excellent; a free text question asking the participants to list 2 ways in which the Rounds will change how they related to or communicate with patients or colleagues; and an open comment section. Textbox 1 shows the Schwartz Rounds evaluation survey.

Schwartz Rounds evaluation.During this session, attendees discussed challenging social and emotional aspects of patient care.Today’s discussion gave me new insights into the perspectives and experiences of my co-workers.Today’s discussion gave me new insights into the perspectives and experiences of patients or families.As a result of this discussion, I feel better prepared to handle tough or sensitive patient situations.As a result of this discussion, I feel less isolated in my work with patients.As a result of this discussion, I feel more open to expressing thoughts, questions, and feelings about patient care with colleagues.I plan to attend Schwartz Center Rounds again.The discussion was well-facilitated.Today’s discussion suggests that changes may be needed in departmental or institutional policies or practices.Today’s program was free of commercial bias.Please rate today’s program overall.List 2 ways in which today’s discussion will change how you relate to or communicate with patients or colleagues (if any):(Example)(Example)Additional comments, including ideas for future topics: (If you would like to share input with the Planning Committee member about your ideas, please provide your name and contact info.)

Focus groups will be conducted after the completion of the Rounds, to give participants the opportunity to provide detailed feedback on the Rounds. Focus groups will be facilitated by an external member of the research team with prior experience in facilitating groups and adequate knowledge of the topic and the purpose of the group. Conversation openers developed by the research team will be used [14-16]. Focus groups will be conducted approximately 2 months after the third Round for each group. Qualitative data will be analyzed thematically by 2 researchers (GH and AT) independently to ensure validity.

### COVID-19 Risk Mitigation Plan

The impact of conducting Rounds in the context of COVID-19 challenges was discussed regularly during the study conception and planning. Research team considered the use of virtual Rounds in the planning stage but decided to proceed with the in-person Rounds, in view of the confidentiality and sensitivity and strong participants’ preference for in-person attendance that was indicated after the pilot Round.

Rounds planning included considerations of the reduced staff participation due to COVID-19–related quarantine, sick and family leave, low staffing levels on Hospital wards, and difficulties in accessing adequate room space to conduct the Rounds safely in accordance with COVID-19 social distancing requirements. The study COVID-19 risk mitigation plan specifies the personal safety and hygiene measures to be followed by the research team and participants, in compliance with Queensland Government and Mater Health COVID-19 guidelines. The measures include social distancing and may include mask wearing and rescheduling of the Rounds during acute lockdowns, in keeping with the government and organizational directives at the time the Rounds are scheduled.

### Safety Considerations

Possible risks to participants include a potential risk of unintended psychological harm to some participants, if they experience emotional distress in response to Rounds content. This risk will be minimized by having 2 researchers (GH and TE) facilitate the Round and 2 members of the research team (JM and AT) attend each Round to focus on participants and monitor for emotional distress. Contact information of the research team will be provided to discuss issues and, an external advisor, experienced in the running of Rounds in Australia, will be engaged in a consultative role. Prior to Rounds, all participants will be given brochures on the Hospital employee assistance program to access counseling and support if needed. In the event of harm occurring through damaged networks with peers or the organization, confidentiality will be emphasized.

### Sample Size and Statistical Power

Participants will be recruited via a convenience sample. The required sample size was calculated using a power calculation for a repeated measures analysis of variance (one group measured across three time points) study using G*Power with effect size of 0.25 (*f*), α level of .05, power of 0.80, and correlation among repeated measures of 0.5. Therefore, it is calculated that a total sample size of 24 will be required for the study to be adequately powered to detect a significant difference (*P*<.05) between the time points. Approximately 10-15 participants will be selected from interested staff, to participate in 2 focus groups. This number of participants will ensure that 5-8 participants will take part in each focus group, in keeping with the recommended size for focus groups, and to ensure an even spread between professions, consistent with previous research recommendations [15,22].

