**Methods:**

This mixed methods repeated measures pilot study will recruit 24 participants in 2 groups from 2 departments, the intensive care unit and the gastroenterology department. Participants from each group will take part in 3 unit-based Schwartz Rounds. Primary outcomes will include the study and intervention feasibility measures, while secondary outcomes will include scores on the Maslach Burnout Inventory–Human Services Survey, the Schwartz Centre Compassionate Care Scale, and the Culture of Care Barometer. Primary and secondary outcomes will be collected at baseline, after the Rounds, and 3-month follow-up. Two focus groups will be held approximately 2 months after completion of the Schwartz Rounds. Descriptive statistics, paired t tests, chi-square tests, and analysis of variance will be used to compare quantitative data across time points and groups. Qualitative data from focus groups and free-text survey questions will be analyzed using an inductive thematic analysis approach.

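### The stated inputs require 28 participants, not 24; with 24 the power is about 74% even if nobody is lost to follow-up

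*Protocol article*

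**What the plan says.** The Sample Size and Statistical Power section reports a G*Power calculation for a "repeated measures analysis of variance (one group measured across three time points"), with "effect size of 0.25" (as f), "α level of .05", power 0.80 and a correlation of 0.5 among the repeated measures. It concludes that "a total sample size of 24 will be required for the study to be adequately powered" to detect a difference between time points.

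The Methods paragraph of the Abstract makes the same number the recruitment target: the study "will recruit 24 participants in 2 groups from 2 departments". The three time points are baseline, after the Rounds, and 3-month follow-up, and they are described consistently in the Abstract and the Methods.

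No allowance for loss to follow-up is stated. The COVID-19 Risk Mitigation Plan reports that planning included "considerations of the reduced staff participation due to" quarantine, leave and low ward staffing.

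**The concern.** The section gives every input the calculation needs except the sphericity correction, so the result can be checked directly. The required number comes out higher than the one stated, and by more than rounding can explain.

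The number serves as both the justification of the sample size and the recruitment target. A reader of a null result on the burnout, compassionate care or culture scores would assume that an effect of f = 0.25 had an 80% chance of being detected. The true chance is lower with complete data and falls further with every incomplete participant. The article also says that the pilot should inform larger studies, so the calculation could be reused.

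**Working it through.** **Inputs** (all from Sample Size and Statistical Power): one group (k = 1), m = 3 measurements, f = 0.25, alpha = 0.05, target power 0.80, correlation rho = 0.5. The sphericity epsilon is not stated. I take epsilon = 1, which favours the plan.

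**Formula.** G*Power's within-factor test uses a noncentral F distribution with

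- lambda = N × m × f² × epsilon / (1 − rho)
- df1 = (m − 1) × epsilon
- df2 = (N − k) × (m − 1) × epsilon

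Power is the probability that this F exceeds the central 5% critical value.

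**Attempt to reproduce 24.** With N = 24 and m = 3, lambda = 24 × 3 × 0.0625 / 0.5 = 9.0, df1 = 2 and df2 = 23 × 2 = 46. Power is 0.741, so the stated figure is not reproduced.

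**The N that the inputs require**

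| Measurements | N | lambda | df | Power |
|---|---|---|---|---|
| 3 | 24 | 9.0 | 2, 46 | 0.741 |
| 3 | 27 | 10.125 | 2, 52 | 0.796 |
| 3 | 28 | 10.5 | 2, 54 | 0.812 |
| 4 | 23 | 11.5 | 3, 66 | 0.797 |
| 4 | 24 | 12.0 | 3, 69 | 0.817 |

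For three measurements, 28 is the first N to reach 0.80. Simulation of the three-measurement design (100,000 trials each) gave 0.743 at N = 24 and 0.812 at N = 28.

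**Does another reading give 24?** These variants keep three time points and the other stated inputs:

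- two groups, time effect: 28
- two groups, group-by-time interaction: 28
- multivariate approach: 29 (one group) or 30 (two groups)
- epsilon 0.75: 34, with power 0.649 at N = 24
- epsilon 0.5: 44
- other conventions for defining f: 53 to 80

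None gives 24. With three measurements, 24 reaches 80% only if a stated input changes: f to about 0.267, rho to about 0.56, or alpha to about 0.075. Four measurements return exactly 24.

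**Effect of incomplete data.** The loss rates below are my assumptions, since the article gives none. The power is for an analysis of participants complete at all three surveys.

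| Loss from 24 | Complete cases | Power |
|---|---|---|
| 0% | 24 | 74% |
| 10% | 21 | 68% |
| 15% | 20 | 65% |
| 20% | 19 | 62% |
| 37.5% | 15 | 51% |

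**The case against.** The strongest reply concerns weight, since nothing in the article supports 24. Feasibility is the primary objective, the powered comparisons are secondary outcomes of an uncontrolled pilot, and the Results section says recruitment is already complete. The Discussion warns that the small sample may leave some outcomes non-significant. The gap is also modest: f of about 0.267 in place of 0.25 closes it, and the article gives no source for either f or the correlation. All of this stands, and it limits the consequence. It does not make the stated number right, and a general caveat about sample size does not tell the reader that the power figure is wrong.

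Two further points deserve credit. The COVID-19 passage is about attending in-person Rounds, whereas the outcome surveys are online, so a missed Round is not a missed survey. The article gives no rate of survey loss and does not say how incomplete cases will be handled. The loss figures are therefore illustrations and are secondary to the main error, which is present with full follow-up. The four-measurement explanation is also an inference; a misreported f, correlation or alpha could equally account for 24.

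**Conclusion.** The concern holds. On the plan's own inputs, 80% power needs 28 participants with complete data. The stated 24 is 4 short (4/28, or 14% of what is needed) and gives 74%, about 6 percentage points below the claim. The 80%-power detectable effect at 24 is f of about 0.27. This rests on epsilon = 1; any nonsphericity correction widens the gap, for example to 65% power at epsilon 0.75 (an assumption). Loss to follow-up lowers power further by an amount the article gives no basis for fixing. No primary conclusion depends on this test, but the statement of adequate power is false as written and should be corrected.

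**What to change.** Delete the claim of adequate power and replace the sentence with, for example: *With 24 participants complete at all three time points, power is about 74% for f = 0.25 (80% for f of about 0.27), assuming sphericity; 28 complete cases would be needed for 80%. If 20% had incomplete follow-up, power would be about 62%.* Label the 20% as an assumption, or replace it with a rate the team can support.

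If 24 came from inputs other than those printed, give the inputs actually used, and make sure that the number of measurements agrees with the three surveys.

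The cost is wording only. The stated power becomes less favourable; the design, recruitment and analysis do not change. If a later study reuses the calculation and wants 28 complete cases, it would need to recruit 32, 33 or 35 for losses of 10%, 15% or 20% (28 / 0.90, 28 / 0.85 and 28 / 0.80, rounded up).

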### Reflexivity to Improve Robustness

Prior to commencing the research, each member of the research team wrote and shared with the team a reflexive statement describing their prior experiences, assumptions, and beliefs about the research process and Schwartz Rounds. These statements will be discussed and revisited in regular research team meetings to enhance the individual researchers and team reflexivity, and the research integrity of the study [32].

In sharing their reflexivity statements, all members of the research team identified that they believed that the Rounds would enhance staff well-being and contribute to more sustained compassionate care and rejuvenated progressive organizational culture. Some members of the research team considered how their dual roles of being a health professional/clinical leader and a member of the research team might affect the research process. It was also acknowledged that, because of the hierarchical nature of the health care system, staff could feel pressured to participate in the Rounds when an operational or clinical manager was promoting the Rounds. Furthermore, concerns about the busy Hospital staff being released to attend the Rounds were identified. These concerns highlighted the importance of the research team members and steering committee communicating regularly with the Hospital executive team and directors of the departments involved in the study to promote the value of the Rounds. Finally, research team members acknowledged that changing organizational culture would take time and that this pilot project would ideally be a springboard for establishing ongoing Rounds in the Hospital.

### Patient and Public Involvement

Views on the study design were obtained during the study conception from the clinical staff working in different departments as well as the nonclinical staff including administrative staff, security workers, human resources staff, and pastoral care. Patient views on the potential benefits of Hospital staff participating in an intervention facilitating compassionate care and staff well-being were elicited through the Hospital Consumer Consultancy Group members. Although the study participants were not formally involved in the recruitment or data analysis, department leaders and other staff members were consulted regarding their departments’ participation.

### Ethics Approval

The study was approved by the Mater Hospital Human Research Ethics Committee (reference number: HREC/MML/71868).

## Results

This study was funded by the Griffith University Health Group collaboration grant in October 2020 and approved by the Mater Hospital Human Research Ethics Committee on January 13, 2021. Recruitment commenced in July 2021 and was completed in September 2021. Data collection commenced in July 2021, with projected completion by March 2022. Data analysis will commence in April 2022 and the results are expected to be published in the second half of 2021. The trail has been registered in the Australian New Zealand Clinical Trials Registry (ACTRN12621001473853).

## Discussion

The key goals of this study are to evaluate the feasibility and efficacy of the Rounds in improving compassionate care, staff well-being, and organizational culture in a tertiary, metropolitan Australian hospital where the cultural background might be different to that of the North American or United Kingdom settings. Although the Rounds are currently being conducted in several other Australian locations, this study is, to our knowledge, the first pilot research study of Schwartz Rounds in Australia.

Another important feature of the study is the Rounds delivery during the current COVID-19–related challenges where this type of staff wellness intervention could be crucial in mitigating staff burnout and improving patient care and organizational culture. Furthermore, the implementation of the Rounds in unit-based format may demonstrate the feasibility and benefits of the Rounds in the most acutely affected departments such as the ICU as well as those with secondary overflow and staffing issues such as the gastroenterology department. Unit-based Rounds may also be more acceptable to staff and more likely to enhance teamwork and sense of shared purpose than the hospital-wide Rounds due to their smaller size and more cohesive group composition.

The use of the mixed methods, combining qualitative data from 2 different sources with quantitative data from the MBI-HHS, SCCCS, and CoCB-v2, will enhance the methodological rigor of the study and the confidence in its findings. The study findings have the potential to provide novel insights into the factors underpinning the feasibility and efficacy of the Rounds and their mechanism of action, and may inform the refinements of the Rounds in future studies.

Key limitations of the study are related to the relatively small sample size and a lack of a control group, which may lead to statistically insignificant findings in some outcome measures and limit the study’s generalizability. However, given the pilot and exploratory nature of the study, its primary role is the assessment of the feasibility of the intervention and study procedures, with qualitative data providing additional valuable insights into these areas.

The results of the one-off pilot Round conducted in January 2021 provided a promising early indication of the potential value of Rounds in Australian settings, and during significant COVID-19–related challenges. The study is, to our knowledge, the first to evaluate Schwartz Rounds in a unit-based format during the COVID-19 pandemic and the first to include the departments potentially acutely affected by COVID-19. We anticipate that the results of the study will have a more wide impact as Schwartz Rounds are increasingly being adopted in different health care settings as well as in universities and other educational settings.

## Abbreviations

CoCB-v2: Culture of Care Barometer – version 2
ICU: intensive care unit
MBI-HHS: Maslach Burnout Inventory–Human Services Survey
SCCCS: Schwartz Centre Compassionate Care Scale
